## Abstract

**Background:**

Older adults living in residential aged care facilities (RACFs), particularly in regional and rural areas, experience a high burden of untreated dental caries, tooth sensitivity, and oral pain. Workforce shortages, limited access to dental services, and competing health priorities make the delivery of timely oral health care challenging in these settings. Poor oral health contributes to pain, impaired nutrition, reduced quality of life, and increased health service use. There is an urgent need for context-appropriate, accessible, and cost-effective interventions for RACF residents. Aqueous silver fluoride (AgF), a minimally invasive topical agent with caries-arresting and desensitizing properties, offers a pragmatic approach suitable for aged care settings.

**Objective:**

This protocol aims to test the effectiveness of an AgF intervention package in reducing tooth sensitivity and tooth pain, arresting caries, and improving oral health and well-being in older adults living in regional and rural RACFs.

**Methods:**

This study is a 2-arm, parallel-group cluster randomized controlled trial, with RACFs as the unit of randomization. The trial is conducted in public and private RACFs across regional and rural Queensland and New South Wales, Australia. Eligible participants are residents with at least 1 natural tooth. At baseline, calibrated examiners perform standardized oral examinations to assess dental caries status, lesion activity, and dentin hypersensitivity. AgF is applied to eligible carious lesions and sensitive tooth surfaces following a standardized clinical protocol. Follow-up assessments at 3 months include a repeat clinical examination to assess caries arrest and changes in hypersensitivity, along with resident-reported measures of oral pain and oral health–related quality of life collected using validated instruments. Outcomes include change in tooth sensitivity and oral pain at the 3-month follow-up, caries arrest rates, and change in oral health–related quality of life. Analyses will follow intention-to-treat principles and account for clustering using mixed-effects regression models with facility-level random effects. Models will adjust for baseline covariates and prespecified confounders. Sensitivity analyses will examine the robustness of the findings. The trial will also inform a planned economic evaluation embedded within the broader research program.

**Results:**

This trial forms part of a broader program funded by the Medical Research Future Fund Dementia, Aging and Aged Care Grant (2024439). Recruitment and data collection commenced in May 2025 and are expected to conclude in June 2026. Recruitment is ongoing across participating RACFs. Data analysis is expected to commence in mid-2026, with primary findings anticipated for publication in early 2027.

**Conclusions:**

This protocol outlines a rigorous evaluation of a minimally invasive, scalable oral health intervention tailored to RACF settings. The findings will provide high-quality evidence on effectiveness to inform policy, service delivery, and economic evaluation aimed at improving oral health and well-being among older adults in residential aged care.

## Introduction

### Background and Rationale

There are specific challenges in identifying and delivering effective treatments that can protect and improve oral health in residential aged care facilities (RACFs). The Australian Royal Commission into Aged Care Quality and Safety Final Report (2021) highlighted the neglect and consequences of oral health in residential aged care, and addressing this area of unmet need is critical [1]. In Australia, residential aged care is provided for older adults who can no longer live independently in their own homes. It includes accommodation and personal care 24 hours a day, as well as access to nursing and general health care services [2].

Older adults living in RACFs have a higher prevalence of poor oral health compared to older people living in the community. This population experiences untreated dental caries, estimated to be as high as 70% [3,4]. In addition, 82% of older adults have gingival recession (root exposure), which is a primary cause of dentin hypersensitivity [3]. Poor oral health causes pain and infection that are associated with major consequences for physical and mental health, including malnutrition, aspiration pneumonia, and cognitive decline [5,6]. Poor oral health can also more broadly impact quality of life by affecting the ability to eat, speak, and engage socially with others [7].

More than two-thirds of RACF residents live with moderate to severe cognitive impairment, further complicating their ability to maintain oral self-care and access conventional dental care [8]. Older Australians residing in RACFs also face various external barriers when accessing dental care. These include financial constraints, organizational barriers, and logistical barriers, which are further exacerbated by the complexity of the aged care system [9-15], particularly for those living in rural and regional areas of Australia. In addition, workforce shortages further restrict the availability of appropriate care [1,14].

Given the barriers to accessing oral health care faced by RACF residents, the use of simple and noninvasive interventions, such as silver fluoride (AgF) application, may offer a practical means to prevent or slow down the progression of oral disease [16]. AgF is a topically applied solution used clinically to arrest active dental caries and prevent further progression of the disease when applied to either the coronal or root surfaces of teeth [17-19]. There are currently 2 types of AgF available in Australia: silver diamine fluoride (SDF) and aqueous AgF. The term AgF will be used in this manuscript as a general umbrella term to encompass the different formulations available.

The literature on AgF in recent years has described the use of various types of AgF products (such as SDF and aqueous AgF) for pediatric and geriatric populations in clinical settings where access to and adherence to conventional treatment can be more challenging. AgF can also be applied in community settings without the need for conventional dental equipment, and application time is quick (1 minute or less) [20]. AgF is easy to use, minimally invasive, painless, meets the immediate needs of the patients, and can be readily implemented in disadvantaged populations due to its low cost [21]. These benefits make it an ideal intervention for older populations, particularly in situations where accessing care is complex due to issues with adherence, mobility, or medical conditions.

The impact of AgF is mainly derived from ionic silver and fluoride ions. As a solution, it has antimicrobial and remineralization actions. It forms insoluble silver precipitates and microwires on the tooth surface that block dentin tubules, reducing sensitivity and making the surface harder [22]. After successful application of SDF, a carious lesion appears with a matte black hardened dentin surface [20]. AgF can also reduce dentin hypersensitivity by depolarizing the cellular membrane of nerve terminals and thereby decreasing nerve responses. A recent systematic review showed that, relative to placebo, SDF can reduce dentin hypersensitivity even after a single application [23]. While SDF is highly effective in arresting and preventing dental caries, its use may be limited due to its ammoniacal smell and potential to irritate the gingivae because of its very alkaline pH [10-12,17-19,21]. Other aqueous formulations of AgF have been developed to reduce such limitations (eg, SDI Riva Aqua AgF with a neutral pH and no ammonia).

SDF has a reported prevented fraction (PF) for caries arrest of 96.1% and 70.3% for caries prevention [19]. The number needed to treat for caries arrest is 0.8, compared to 3.7 for fluoride varnish, while the number needed to treat for caries prevention is 0.9 compared to 1.1 for fluoride varnish [19]. For root caries prevention, the estimated PF was 25% to 71% higher for SDF than for placebo [17-19]. Similar findings for caries arrest and caries prevention for coronal tooth surfaces have been reported. The PF was 70% to 78% and 55% to 96% for coronal caries prevention and arrest, respectively [18,19]. In a more recent study assessing clinical efficacy, aqueous AgF was found to have clinical effectiveness in arresting smooth surface dental caries greater than 90% [24].

In the present study, a stabilized aqueous AgF formulation (Riva Star Aqua, SDI Ltd., Australia) containing 38% AgF will be used [25]. This is comparable to concentrations historically used in Australian public dental programs [26,27] and supported by recent clinical evidence demonstrating high predictability (92%) for arresting active carious lesions [24,28].

### The Gap in Current Knowledge

*The neglect of oral health in residential aged care was among the many terrible stories we heard over months of hearings in 2019. Poor oral health is very serious medically because it can contribute to chronic medical conditions, as well as to severe pain, discomfort, functional impairment and restrict an older person’s ability to eat, speak and socialize.* [1]

Oral health is fundamental to the quality of life in older adults [29,30]. Freedom from unnecessary pain and suffering is a basic human right, and access to essential oral health care should be regarded within this framework [29]. Poor oral health in RACFs contributes not only to individual suffering but also to the broader health system burden through increased medical complications and avoidable treatment needs.

Despite this, conventional dental care remains costly, episodic, and often inaccessible for disadvantaged older adults, particularly those residing in rural and regional RACFs. There is a clear need for simple, scalable, low-burden, and cost-effective interventions that can be delivered within aged care settings.

AgF represents a promising solution. It is inexpensive (US $0.71 per tooth) [31], noninvasive, and can arrest dental caries without requiring complex restorative procedures. However, robust evidence evaluating its effectiveness, feasibility, and implementation specifically among older adults living in RACFs remains limited. A targeted study in this population is therefore urgently needed to inform policy and practice in aged care oral health.

### Objectives

This study aims to evaluate the effectiveness of the AgF intervention in reducing tooth sensitivity and dental pain, arresting dental caries, and improving oral health and well-being among older adults residing in regional and rural RACFs. The study will also assess the economic impact and scalability of the intervention within aged care settings.

This study has the following objectives:

To evaluate the efficacy of a tailored AgF intervention in arresting caries and reducing dental pain and sensitivity among older adults in RACFsTo evaluate the efficacy of the AgF intervention in improving normal daily life activities and oral health–related quality of lifeTo evaluate the cost-effectiveness and cost-utility of the interventionTo evaluate scalability and facilitate the implementation of the developed full intervention package

## Methods

### Trial Design

This study is part of a larger aged care full intervention package that assesses a combination of a modified oral health assessment tool (M-OHAT), standardized RACF staff training and education in using this assessment tool, standardized oral examination by an oral health professional, and an AgF intervention package to benefit the health and well-being of residents in RACFs. This study is designed as a cluster randomized controlled trial. RACFs serve as the unit of randomization, and individual residents as the unit of analysis. The control arm will receive a delayed intervention because of existing clinical equipoise regarding the effectiveness of AgF applications in reducing dentin hypersensitivity.

### Recruitment and Flow of the Study

Public and private aged care providers located in regional and rural Queensland and New South Wales, Australia, will be identified, approached, and provided with a Facility Participation Information and Consent Form prior to enrollment as study clusters. Once RACFs have consented, they will be randomly allocated in a 1:1 ratio to either the intervention or control arm using a computer-generated random sequence. Clusters assigned to the intervention arm will receive the AgF intervention at the first clinical visit, while those in the control arm will be offered the intervention after a 3-month delay. All individuals within a cluster will receive the same allocation condition. Study information materials, including leaflets and a short explanatory video, will be provided to participating RACFs for distribution within their facilities. Facility staff will identify and approach potentially eligible residents and coordinate scheduling with the study coordinator.

Upon arrival at the facility, the research team will meet with residents (and, where applicable, their Enduring Power of Attorney) to provide a detailed explanation of the study, confirm eligibility, and obtain written informed consent. Where there are any communication difficulties, RACF staff will be engaged to assist with facilitating communication. Once written informed consent has been obtained, the research team will administer a questionnaire, conduct an oral examination, and administer the AgF intervention in accordance with the study protocol.

For individuals requiring urgent dental care or identified as high risk of rapid oral health deterioration, regardless of their allocation, RACF staff will be advised by the research team clinicians, and referral will be made to their care facility to initiate appropriate action to access dental treatment. This does not exclude individuals from participating in the study.

At 3 months, the study coordinator will coordinate follow-up assessments with participating facilities. Ongoing consent will be confirmed with participants (and, where applicable, their Enduring Power of Attorney) prior to follow-up procedures.

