### Intervention

AgF will be the intervention treatment used in this study. The first of the 2 bottles of the SDI Riva Star Aqua system (manufactured by Southern Dental Industries Ltd.), which contains 38% aqueous AgF, will be applied. This corresponds to step 1 of the manufacturer’s 2-step procedure. The decision to use only the first bottle is intended to simplify the application process and reduce treatment time. Using the first bottle of AgF ensures the evidence is relevant for generic AgF products, which is important for wider implementation of the findings.

At time 1 (the initial appointment, T1), all consented participants will undergo an oral examination to assess oral conditions and identify teeth requiring AgF treatment.

In an oral environment with a high risk of caries (eg, salivary gland hypofunction, acidic mouth pH), root surfaces and exposed dentin are at increased risk of dental caries developing. For participants assessed as being at high-risk of oral health issues developing, referral and discussion with the nurse coordinator at the facility will be undertaken as appropriate.

Participants in the intervention group will receive AgF during this first appointment. In contrast, participants in the control group will receive the same treatment at the 3-month follow-up appointment. AgF will be applied by the research team’s trained oral health professionals.

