### Blinding to Intervention

In accordance with the CONSORT (Consolidated Standards of Reporting Trials) 2025 guidelines for cluster randomized trials [35], blinding will be implemented where feasible to minimize bias. As the AgF application leaves a distinct black stain on carious lesions, this may inadvertently reveal allocation status to participants, RACF staff, and treating clinicians. Therefore, no attempt will be made to blind the clinical team. To mitigate bias in outcome assessment, both site identity and treatment allocation will be blinded during data analysis. A detailed statistical analysis plan will be finalized, and analysis syntax prepared, prior to data availability. Data analysts will receive deidentified datasets with anonymized group labels (eg, Group A and Group B), and the allocation decoding key will be securely retained by the project lead until primary analyses are completed.

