### Resident Participant Timeline

Table 1 presents the participant timeline for the cluster randomized controlled trial of AgF, including the intervention and control groups. Residents who elect to participate will be invited to provide informed consent. At baseline (T1), all participants will receive an oral health assessment and complete a demographic, quality of life, and oral health survey (Table 1). Those allocated to treatment will also receive an AgF application. At the 3-month follow-up, all participants will receive the oral health assessment and survey again; control group participants will receive the AgF application.

**Table 1. T1:** Resident participant timeline for the cluster randomized controlled trial of silver fluoride, showing intervention group and control group.

Procedures	Study period		
	Enrollment	T1	T2
Enrollment			
Consent (self, legal guardian, or NCAT^a^, QCAT^b^)	✓		
Exclusion criteria	✓		
Allocation (cluster)	✓		
Survey			
Demographics and oral health history		✓	✓
Quality of life (EQ-5D-5L) [36]		✓	✓
Geriatric Oral Health Assessment Index (GOHAI) [37]		✓	✓
Intervention			
Intervention clusters: AgF applications for clinically indicated teeth at T1		✓	
Control clusters: AgF applications for clinically indicated teeth at T2			✓
Summary of data collection			
Oral clinical assessment (dental caries experience; dentin exposure; tooth sensitivity; oral hygiene status; oral mucosal conditions; salivary status)		✓	✓
Oral health–related quality of life		✓	✓
Quality of life		✓	✓
Demographics	✓		
General health, medications, and diet		✓	✓
Health economic information: cost and referral uptake		✓	✓
Health economic information: participant experience		✓	✓

a NCAT: NSW Civil and Administrative Tribunal.

b QCAT: The Queensland Civil and Administrative Tribunal.

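### Facilities are allocated before residents are approached, consented and examined, and the only blinding step, at analysis, cannot mitigate bias in outcome assessment as the article claims

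*Protocol article*

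**What the plan says.** All places are in the protocol article.

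- **Order of steps (Recruitment and Flow of the Study).** "Once RACFs have consented, they will be randomly allocated in a 1:1 ratio to either the intervention or control arm". The section then turns to residents: "Facility staff will identify and approach potentially eligible residents and coordinate scheduling with the study coordinator". Eligibility and consent follow at the visit: "Upon arrival at the facility, the research team will meet with residents". After that, "Once written informed consent has been obtained, the research team will administer a questionnaire, conduct an oral examination, and administer the AgF intervention".
- **First visit (Intervention).** At T1 "all consented participants will undergo an oral examination to assess oral conditions and identify teeth requiring AgF treatment". One examination thus supplies both the baseline and the treatment indication. "Participants in the intervention group will receive AgF during this first appointment", while controls are treated at 3 months.
- **Blinding (Blinding to Intervention).** The clinical team is left unblinded, and the reason given is the black stain that AgF leaves on carious lesions. The stated countermeasure is: "To mitigate bias in outcome assessment, both site identity and treatment allocation will be blinded during data analysis".
- **Other safeguards.** Inclusion and Exclusion Criteria has every eligible permanent resident invited, with no symptom or caries requirement, but excludes those who decline examination or treatment. Oral Health Assessment describes a standardized protocol and calibration. Oral Health Status specifies intention-to-treat analysis and adjustment for the baseline value of each outcome.

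**The concern.** Cluster randomization protects the comparison only if residents enter, and their baseline is recorded, independently of the arm. Here both come after allocation.

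There are two routes to a difference between arms. The first is consent: the offer is immediate treatment in one arm and delayed treatment in the other, and declining treatment is an exclusion. The second is T1 recording. Hypersensitivity at the tooth level rests on self-report or an observed reaction to air, and the lesions charted at T1 are those whose arrest can later be judged.

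The article answers assessment bias with analyst blinding. That limits discretionary choices in the analysis. It cannot change values that an unblinded team has already recorded. The stain does not explain an open baseline either, because the T1 examination comes before AgF is applied.

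**Working it through.** **Who can know the arm, and when**

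| Step | Place in the article | Knowledge of the arm |
|---|---|---|
| Facility allocated | Recruitment and Flow | Allocation exists |
| Residents approached by facility staff | Recruitment and Flow | Inferred from the order; not stated |
| Consent, survey, T1 examination | Recruitment and Flow; Intervention | Team unblinded; no step withholds the arm |
| AgF in one arm only | Intervention | Team must know |
| Analysis | Blinding to Intervention | Coded group labels |

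Table 1 is consistent with this but does not settle it. It lists consent, exclusion criteria and cluster allocation in one enrollment column, so it shows allocation before T1 but not before resident consent.

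**The plan's own precision.** Sample Size Calculation gives 28 clusters (14 per arm), 25 completers each and ICC 0.15.

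- Design effect = 1 + 24 × 0.15 = 4.6. Effective n per arm = 350 / 4.6 = 76.1.
- Detectable effect at 80% power, two-sided 0.05 (sidedness assumed): 0.454 SD (normal) or 0.472 SD (t, 26 df). Power at the stated 0.48 is 0.813, so that figure reproduces.
- The stated 0.20 SD reproduces as 0.198 (t) with individual autocorrelation 0.5, baseline adjustment and an assumed cluster autocorrelation of 1.

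**Bias under the planned model.** The adjusted effect is D2 − b × D1. D1 and D2 are the AgF-minus-control differences at T1 and T2 with no true effect, and b is the slope of T2 on T1. Higher scores are worse, so a negative value favors AgF. The document gives neither D1 nor b. Assume D1 = 1 unit on the visual analog scale and b = 0.5.

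| Mechanism | D2 | Adjusted effect | Direction |
|---|---|---|---|
| T1 inflated, not carried to T2 | 0 | 0 − 0.5 × 1 = −0.5 | Toward AgF |
| Selection on observed T1 only | 0.5 | 0.5 − 0.5 × 1 = 0 | None |
| Entrants stably worse at T1 and T2 | 1 | 1 − 0.5 × 1 = +0.5 | Against AgF |

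In SD units, 0.5 / 2.6 = 0.19. If b runs from 0.3 to 0.7, the first row runs from 0.3 to 0.7 unit (0.12 to 0.27 SD) toward AgF, and the third from 0.7 to 0.3 unit against it. Halving D1 halves each figure.

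**Benchmarks.** 0.19 SD is close to the 0.20 SD detectable effect and well below 0.48 SD. Half a unit is 0.5 / 2.9 = 17% of the planning difference.

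**False rejection with no true effect, for an assumed bias**

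| Bias | Precision implied by 0.48 | Precision implied by 0.20 |
|---|---|---|
| 0.10 SD | 9.0% | 28.8% |
| 0.20 SD | 21.5% | 80.0% |

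More clusters narrow the interval around the biased value; they do not move it.

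The scale used here is resident-reported and was chosen because it is the only outcome with an SD in the document. A T1 inflation on it would come through the resident, proxy or assisted survey. Examiner charting concerns the tooth-level outcomes, for which no SD is given.

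**The case against.** The strongest reply is that the article has more protection than analyst blinding. Inviting all eligible residents leaves little room, on paper, for staff to put forward those with dental problems. Calibration and a standardized protocol discipline the examination. Baseline adjustment deals with differences in observed T1 severity. Nowhere does the article say that staff, residents or proxies are told the arm before consent, and a condensed article may leave concealment procedures to the full protocol.

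Most of this stands, and it rules out three stronger readings.

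- A reader might infer that blinding at analysis is the only control on bias. It is the only blinding step; the other safeguards are real.
- A reader might infer that staff selected residents knowing the arm. The order of steps permits this, but no sentence states it.
- A reader might infer that sicker entrants in the AgF arm would regress to the mean and mimic benefit. That applies to an unadjusted change score. The planned adjustment largely removes it, as the second row of the bias table shows.

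What remains does not depend on omitted detail. An invitation to all does not equalize who accepts. Calibration reduces variation between examiners but not their knowledge of the arm. Adjustment takes the T1 value as given, so it cannot repair one recorded with knowledge of the arm, nor correct unmeasured selection at consent. The claim about analyst blinding is in the text and is wrong as written.

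**Conclusion.** The point holds in a limited form. Allocation precedes resident recruitment, the team that examines and treats at the first visit is unblinded, and the reason given for this does not apply to the T1 examination. The statement that blinding at analysis mitigates outcome-assessment bias is incorrect.

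Whether bias has occurred, and which way it runs, cannot be told from the document. With an assumed 1-unit T1 difference and slope of 0.5, the planned model gives anything from 0.5 unit toward AgF, through about 0, to 0.5 unit against it. The document therefore does not support saying that the trial is biased in favor of AgF. It supports saying that the design leaves room for a bias of about the size of the smaller detectable effect, and that the stated remedy does not address it.

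**What to change.** 1. For facilities whose arm has not been disclosed, release the allocation to the facility and field team only after consent, survey and T1 examination are entered. AgF already follows the examination in the visit sequence.
2. At remaining T2 visits, collect the visual analog scale, pain, GOHAI and EQ-5D-5L before the examination and without the T1 chart at hand.
3. For all facilities, report eligible, approached and consented residents by arm.
4. In Blinding to Intervention, replace the sentence on outcome-assessment bias with a statement that analyst blinding limits analytic choices only, and that recruitment and assessment were open.

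**Cost.** Scheduling becomes less predictable, because the team learns on site whether it will treat; no extra staff are needed. Early and late facilities would differ in procedure, which should be recorded. The T1 benefit reaches few sites: by February 2026, 25 facilities were enrolled out of a target of 28, and about 20 had completed both visits. That leaves 3 still to enroll and about 5 enrolled but unfinished, some of which may already know their arm. Items 3 and 4 apply whatever the stage of recruitment.
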